**Fig. 3 Fig3:**
[figure not shown]
Summary of assessments at baseline and follow-up

Participants can discontinue trial treatment at any time but can remain in the trial, taking Week 2 vaginal samples and completing all follow-up questionnaires. They can also withdraw from the follow-up assessments at any time.

### Qualitative telephone interviews

A subgroup of participants will be contacted for semi-structured telephone interviews to explore acceptability and adherence to trial treatment, and how these can be optimised. A random sample of participants who gave optional consent to be contacted will be recruited until initial analysis suggests data saturation. The sample size will then be reviewed to check that it is representative of the trial target population in terms of age, ethnicity, recruiting site and number of BV episodes. Where necessary, further participants will be recruited to ensure a diverse spread of the target population. The final sample size is expected to be approximately 30 participants (15 in each trial arm). Interviews will be audio recorded, transcribed and uploaded into NVivo to assist with data management. Transcripts will be coded and analysed thematically.

### Collection and analysis of vaginal samples

At the baseline visit, participants will be provided with a kit for taking their own vaginal samples at Week 2. The central laboratory will perform the following tests on vaginal samples taken at baseline and at Week 2: microscopic assessment of BV; nucleic acid amplification tests for chlamydia, gonorrhoea and trichomoniasis. Results will be returned within 1–2 months for the recruiting site to review (investigator and research nurse) and to arrange further testing or treatment according to local protocols. These trial tests will not form the basis for patient management at the baseline visit; clinicians will take additional tests processed locally to inform immediate patient care as indicated by the patient’s clinical presentation.

### Adverse events and pregnancy reporting

The safety profiles of the treatments in this trial are well characterised. Metronidazole is being used for its licensed indication and lactic acid gel is being used within its intended use covered by the CE mark. In order to provide secondary outcome data to compare tolerability of the two treatments, specified adverse reactions experienced during trial treatment will be reported. The following are regarded as expected for the purpose of this trial and will be reported on the Week 2 questionnaire completed by the participant: nausea, vomiting, taste changes, vaginal irritation, abdominal pain, diarrhoea. Serious adverse events are not anticipated in this low-risk trial but will be recorded if reported by participants.

Although lactic acid gel is considered safe for use in pregnancy and metronidazole is frequently prescribed for treatment of BV in pregnancy, patients will be asked to confirm that they are not pregnant as part of the screening process. Participants will also be asked to confirm their pregnancy status during their follow-up period. Any pregnancies reported during the period between randomisation and Week 2 will be followed up for outcomes.

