### Participants

The flow of participants from presentation through to follow-up is shown in Fig. 2. Inclusion criteria are as follows: age 16 years or over; clinical diagnosis of BV based on patient-reported symptoms of discharge with an unpleasant (typically fishy) odour (with or without positive microscopy according to local site practice); history of at least one previous episode of BV within the past 2 years (clinically diagnosed or patient reported) which resolved with treatment; willing to use either intravaginal lactic acid gel or oral tablets for the management of BV; willing to take own vaginal samples; willing to avoid vaginal douching during treatment; willing to provide contact details and be contacted for the purpose of collecting follow-up information; willing to avoid sexual intercourse or use effective contraception for the 7-day duration of study treatment (condoms are not considered to be effective contraception due to a potential interaction with lactic acid gel); access to the Internet and email and willing to complete web-based follow-up questionnaires in English; provision of written informed consent.

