#### Lactic acid gel

There is no SmPC for lactic acid gel, but the following should be noted:
Shellfish allergy: Some lactic acid gel brands may contain glycogen obtained from oysters.Condom use: The effects of lactic acid gel on condom degradation have not been fully determined. Therefore, it is advised that condoms should not be assumed to be an effective method of contraception during the 7-day treatment period with lactic acid gel.

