### Dosing schedule

Treatment should be started on the day of receipt, but participants will be instructed to record their actual start date and time (morning or evening) of dosing in their patient diaries. Participants will also be asked to use their patient diaries to log all subsequent doses taken and/or missed doses over the treatment period in order to aid compliance to the treatment schedule.

No treatment or dose modifications are expected in this trial. Where a dose is accidentally missed, participants will be advised to follow the manufacturer’s instructions or seek advice from their physician. In the case of any missed dose, participants will be advised to continue to complete their treatment course.

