### Trial assessments and procedures

All assessments and procedures to be performed at each time point for participants are indicated in Fig. 3. Most assessments will be done at baseline, including demographics, symptoms and previous BV episodes, medical and sexual history, concomitant medications, contraception and condom use, SF12™ Health Survey and vaginal samples for BV/STI screening (sites will send the baseline samples to a central laboratory at University Hospitals Birmingham NHS Foundation Trust which is accredited under the UK Accreditation Service to perform the tests). After randomisation into the trial, participants will then take their first dose of trial treatment and continue taking trial treatment for 7 days. At Week 2, participants will take their own vaginal samples and send them to the central laboratory. They will also complete a web-based questionnaire with details of symptoms, treatment adherence and tolerability, any known side effects, healthcare use, additional BV treatments, sexual history, contraception/condom use and another SF12™ Health Survey. Participants will be asked to complete a further two web-based questionnaires at 3 months and 6 months with details of BV recurrence, sexual history, healthcare use, additional BV treatments, contraception/condom use and a final SF12™ Health Survey (6 months only). Those not responding to requests to complete web-based questionnaires will be contacted by phone and/or text to collect follow-up data.

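### Pregnancy outcome follow-up is triggered by the date of report rather than of conception, so many or all pregnancies conceived during the 7 treatment days could fall outside it

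*Protocol article*

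**What the plan says.** The section Adverse events and pregnancy reporting makes three statements about pregnancy.

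- At screening: "patients will be asked to confirm that they are not pregnant as part of the screening process". No pregnancy test is mentioned.
- Afterwards: "Participants will also be asked to confirm their pregnancy status during their follow-up period". Follow-up runs to 6 months.
- On outcomes: "Any pregnancies reported during the period between randomisation and Week 2 will be followed up for outcomes". Nothing is stated about the outcomes of pregnancies reported later.

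The treatment period is fixed elsewhere. Under Trial assessments and procedures, "participants will then take their first dose of trial treatment and continue taking trial treatment for 7 days"; under Dosing schedule, "Treatment should be started on the day of receipt". Treatment supplies, labelling and storage allows primary care participants to collect a prescription from any pharmacy, so receipt can come after randomisation.

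Conception during treatment is something the protocol itself guards against. Under Participants, women must be "willing to avoid sexual intercourse or use effective contraception for the 7-day duration of study treatment", with the note that "condoms are not considered to be effective contraception due to a potential interaction with lactic acid gel". The section on lactic acid gel adds: "The effects of lactic acid gel on condom degradation have not been fully determined".

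**The concern.** A window that closes at Week 2 suggests that the aim is to learn what happens to pregnancies that overlap with treatment. A rule based on the date of report serves that aim only if such pregnancies are recognised and reported before the window closes. Those conceived in the treatment week are the least likely to be, because they are at most two weeks old at nominal Day 14. Someone applying the sentence exactly would have no instruction to follow up a pregnancy first reported at 3 or 6 months, even if its dates put conception inside the treatment week.

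What is at stake is the completeness of a small piece of safety information. The trial could have followed few or no outcomes of pregnancies conceived on treatment while its later follow-up data contain such pregnancies.

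**Working it through.** The protocol gives no figure for this point, so there is none to reproduce. The check is a timing calculation.

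**Inputs from the protocol article**
- Treatment duration: 7 days (Trial intervention; Trial assessments and procedures).
- Close of the window: Week 2, taken as nominal Day 14 (Adverse events and pregnancy reporting).
- Start of treatment: day of receipt (Dosing schedule).

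**Assumptions, not in the document**
- Start delay s after randomisation: 0 or 3 days.
- Lag D from conception to a pregnancy the woman can recognise: 10, 12, 14 or 16 days.
- Given a conception during treatment, its day is uniform over the 7 days.
- Week 2 report received on day w: 14 if on time, 21 if a week late.

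**Age of the pregnancy at the report**

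A conception falls between day s and day s + 7, so its age on day w lies between w − (s + 7) and w − s.
- w = 14, s = 0: 7 to 14 days.
- w = 14, s = 3: 4 to 11 days.

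**Share recognisable at the report**

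A pregnancy is recognisable if conception was no later than day w − D. Under the uniform assumption:

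share = (w − D − s) / 7, limited to the range 0 to 1.

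Report on Day 14, same-day start:
- D = 10: (14 − 10 − 0)/7 = 4/7 = 57%
- D = 12: 2/7 = 29%
- D = 14: 0/7 = 0%
- D = 16: negative, so 0%

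Report on Day 14, 3-day delay:
- D = 10: (14 − 10 − 3)/7 = 1/7 = 14%
- D = 12, 14 or 16: negative, so 0%

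Report on Day 21, same-day start:
- D = 10, 12 or 14: the ratio is 1 or more, so 100%
- D = 16: (21 − 16 − 0)/7 = 5/7 = 71%

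Report on Day 21, 3-day delay:
- D = 10: 8/7, so 100%
- D = 12: 6/7 = 86%
- D = 14: 4/7 = 57%
- D = 16: 2/7 = 29%

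**Reading the results**

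With reports on time, the rule misses at least 43% of pregnancies conceived during treatment in the most favourable case (100% − 57%), and all of them once D reaches 14 days. A report one week late recovers most or all of them for a same-day start. It would count only if a late Week 2 questionnaire is treated as falling within the period up to Week 2, which the article does not settle.

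The expected number of such pregnancies cannot be calculated, because the article gives neither contraceptive use nor a conception rate.

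**The case against.** The case on the other side has several parts, and much of it stands.

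- *Some exposed pregnancies are inside the rule.* A reader might infer that every pregnancy exposed to treatment is missed. The documents do not support that. Screening rests on the woman's own confirmation, so a pregnancy can be present but unrecognised at randomisation. It would then be exposed, and it can well be reported by Week 2.
- *Later pregnancies are still recorded.* A reader might also infer false reassurance about condom failure. That risk concerns whether pregnancies occur, and pregnancy status is asked during follow-up, so the counts remain available. Only the outcomes are lost.
- *Eligibility already limits the condom route.* Condoms do not count as effective contraception during treatment, and women trying to conceive are excluded. This reduces the number of cases but does not remove them, since the criterion is willingness rather than verified use.
- *The recognition lag is an outside assumption.* A reader might conclude that no such pregnancy can be known by Week 2. That follows only for a lag of about 14 days or more with on-time reporting. Non-responders are contacted by phone or text, so late Week 2 reports are foreseeable and would catch more.
- *The protocol describes a low-risk setting.* It calls the gel safe in pregnancy and notes that metronidazole is often prescribed for BV in pregnancy. This limits the seriousness of the point.
- *The sentence may be shorthand for pregnancies occurring by Week 2.* A journal article condenses the full protocol, so this is possible. But the article does state a rule, and the word it uses is reported. If occurrence was meant, the correction is the same.

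**Conclusion.** The point holds in a limited form. As written, outcome follow-up depends on the date of report, and the window closes when a pregnancy conceived during treatment is only 7 to 14 days old, or 4 to 11 days old with a 3-day start delay. With on-time reports, the share that could be known by then is 57%, 29% or 0% for an assumed recognition lag of 10, 12 or at least 14 days after a same-day start, and 14%, 0% or 0% after a 3-day delay. Many or all of these pregnancies would therefore first be reported when no outcome follow-up is stated.

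These shares rest on the assumed lags, on conception days spread evenly over treatment, and on Week 2 meaning Day 14. The loss is confined to outcomes of pregnancies conceived during treatment, probably few in number. The primary outcome, the sample size and the planned efficacy comparisons are unaffected.

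**What to change.** Reword the rule so that outcome follow-up applies to any pregnancy whose estimated conception date is before the end of the Week 2 window, including those already present at randomisation, whenever it is reported during the 6-month follow-up. State the last day of the Week 2 window so that the rule can be applied consistently.

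Add one dating field, last menstrual period or due date, to the existing follow-up pregnancy question, so that later reports can be classified.

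The cost is one sentence, one questionnaire field and outcome enquiries for a few more pregnancies. Some of these will end after the 6-month follow-up and will need a contact beyond it. The cut-off at the end of the Week 2 window also takes in some conceptions after the last dose. That is a modest excess, and it keeps the rule simple where the treatment start date or the dating is uncertain. No treatment, eligibility or contraception requirement changes.

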### Data management

All trial data will be entered on a trial-specific database through the electronic Case Report Form (eCRF) with participants identified only by their unique trial number and initials. The database will be developed and maintained by the NCTU. Access to the database will be restricted and secure, and all data transactions will be logged in a full audit trail.

The NCTU will check site-completed eCRFs for compliance with the protocol, data consistency, missing data and timing. Sites will be asked for missing data or clarification of inconsistencies or discrepancies.

### Statistical considerations

#### Analysis of outcome measures

The analysis and reporting of the trial will be in accordance with Consolidated Standards of Reporting Trials (CONSORT) guidelines. A full Statistical Analysis Plan will be developed and agreed prior to database lock and unblinding of the analysing statistician. Continuous variables will be summarised in terms of the mean, standard deviation, median, lower and upper quartiles, minimum, maximum and number of observations. Categorical variables will be summarised in terms of frequency counts and percentages. Descriptive statistics of demographic and clinical measures will be used to assess balance between the randomised arms at baseline, but no formal statistical comparisons will be made.

The primary approach to between-group comparative analyses will be by the modified intention-to-treat method, i.e. including all participants who have been randomised and without imputation of missing outcome data. Sensitivity analyses will be conducted to investigate the impact of missing data and adherence to treatment.

The evaluation of the primary outcome will be performed using a mixed effects model for binary outcome that includes factors used in the minimisation. The comparison of lactic acid gel with oral metronidazole will be presented using the risk difference in the proportion of participants who reported resolution of symptoms at Week 2, along with the 95% confidence interval (CI).

Secondary outcomes will be analysed using appropriate regression models dependent on data type (binary, continuous, count, survival, etc.) and will include factors used in the minimisation and baseline value of the outcome where measured. The analyses of secondary outcomes will be considered supportive to the primary, and estimates and *p* values, where presented, should be interpreted in this light.

Presentation of quantitative tolerability data will be descriptive. Frequency counts and percentages of the proportion of participants reporting nausea, vomiting, taste disturbance, vaginal irritation, diarrhoea and abdominal pain will be presented by treatment arm.

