## Methods/design

### Aims and objectives

The trial hypothesis is that intravaginal lactic acid gel is clinically effective and cost effective in the treatment (i.e. resolution of symptoms) of women with recurrent BV compared with oral metronidazole. The aim is to test this hypothesis by comparing symptom resolution in the intervention group (receiving intravaginal lactic acid gel) with the control group (receiving oral metronidazole) for women with recurrent BV.

The primary objective of the trial is to determine whether intravaginal lactic acid gel is better than oral metronidazole for symptomatic resolution of recurrent BV. Secondary objectives include the following: comparing the time to first recurrence of BV symptoms; comparing the frequency of BV episodes over 6 months; comparing the frequency of BV treatments required over 6 months; comparing microbiological resolution of BV on microscopy 2 weeks after presentation; comparing the tolerability profiles of lactic acid gel and metronidazole; comparing adherence to lactic acid gel versus metronidazole tablets; comparing acceptability of use of lactic acid gel versus metronidazole tablets; determining comparative presence of concurrent sexually transmitted infections (STIs) at baseline and at Week 2; comparing quality of life (measured using the SF-12™ Health Survey [21]); comparing the cost effectiveness of using intravaginal lactic acid gel versus oral metronidazole tablets. In addition, samples for further microbiological analysis, including gene sequencing, will be collected for future investigation into the factors associated with successful treatment.

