### Outcome measures

The primary outcome is resolution of BV based on participant-reported resolution of symptoms at Week 2. Secondary outcome measures are as follows: time to first recurrence of BV; number of participant-reported BV episodes over 6 months; number of participant-reported BV treatment courses over 6 months; microbiological resolution of BV on microscopy of vaginal smears at Week 2; comparative tolerability of lactic acid gel and metronidazole assessed by web-based participant reporting of side effects (including nausea, vomiting, taste disturbance, vaginal irritation, diarrhoea and abdominal pain) and via participant telephone interviews; participant-reported adherence to treatment; acceptability of treatments via qualitative assessment in a subgroup of participants; prevalence of concurrent STIs (gonorrhoea, chlamydia and trichomoniasis) at baseline and at Week 2; quality of life as assessed by SF-12™ Health Survey at baseline, Week 2 and 6 months; comparative cost effectiveness of using intravaginal lactic acid gel versus oral metronidazole tablets via National Health Service (NHS) Service use questionnaire.

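### Tolerability is a comparative secondary outcome, but the plan reports only counts and percentages by arm, with no between-arm estimate or interval

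*Protocol article*

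**What the plan says.** The protocol article presents tolerability as a comparison in three places.

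- Under Aims and objectives, one secondary objective is "comparing the tolerability profiles of lactic acid gel and metronidazole".
- Under Outcome measures, a secondary outcome is "comparative tolerability of lactic acid gel and metronidazole assessed by web-based participant reporting of side effects", supplemented by telephone interviews.
- Under Adverse events and pregnancy reporting, the reason given for collecting the specified reactions is "In order to provide secondary outcome data to compare tolerability of the two treatments". The six reactions are recorded by the participant on the Week 2 questionnaire.

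Analysis of outcome measures first sets a general rule: "Secondary outcomes will be analysed using appropriate regression models dependent on data type", with the minimisation factors and, where measured, the baseline value included. It adds that "The analyses of secondary outcomes will be considered supportive to the primary", and that estimates and p values, where given, are to be read in that light. The paragraph that follows treats tolerability differently: "Presentation of quantitative tolerability data will be descriptive". The planned output, split by arm, is "Frequency counts and percentages of the proportion of participants reporting nausea, vomiting, taste disturbance, vaginal irritation, diarrhoea and abdominal pain". No effect measure or interval is named for it.

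**The concern.** An outcome defined as a comparison between arms would normally be summarised by an estimate of the between-arm difference and its uncertainty. Here the plan stops at the two columns of percentages. This is a stated choice of method and not silence that a later analysis plan would fill, so an analysis plan that follows the article would report no tolerability estimate.

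The outcome matters to how the trial will be used. The Abstract and Background give antibiotic side effects as part of the case for looking beyond metronidazole, and the Background says the trial will assess whether the gel is effective and well tolerated. The efficacy question is framed as superiority. If superiority is not shown, side effects are likely to weigh heavily in the treatment choice and in the guidelines that the trial hopes to inform. The contrast with Planned subgroup analyses is also awkward: exploratory subgroups are promised between-group effects and an interaction with 95% CI, while this named secondary outcome is promised neither an effect nor an interval.

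**Working it through.** **Inputs.**

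- Analysed participants: 1710, from Power calculation/sample size calculation. With 1:1 allocation (Randomisation) this is 855 per arm. Side effects and the primary outcome are both reported by the participant at Week 2, so 855 is a reasonable planning denominator for both.
- Side-effect rates: the article gives none. All rates below are assumptions.

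**Step 1: reproduce the plan's own figure.** For 80% v 86%, two-sided 5%, 90% power, the pooled formula gives

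n = [1.960 × √(2 × 0.83 × 0.17) + 1.282 × √(0.80 × 0.20 + 0.86 × 0.14)]² / 0.06² = 821.6, that is 822 per arm.

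With the continuity correction,

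n′ = (n/4) × [1 + √(1 + 4/(n × 0.06))]² = 854.6, that is 855 per arm and 1710 in total.

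Allowing for 10% non-collection, 1710 / 0.90 = 1900. Both stated figures reproduce, and nothing in this point disputes them.

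**Step 2: precision available for a side-effect difference.** At a common rate p, the Wald 95% half-width is 1.96 × √(2p(1 − p)/855).

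| Assumed common rate | Half-width (percentage points) |
|---|---|
| 2% | 1.3 |
| 5% | 2.1 |
| 10% | 2.8 |
| 20% | 3.8 |
| 30% | 4.3 |
| 40% | 4.6 |

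The trial is large enough for such intervals to be informative, so sample size is no reason to leave them out.

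**Step 3: what the percentages alone would not show.** With unequal rates the half-width is 1.96 × √([p₁(1 − p₁) + p₂(1 − p₂)]/855).

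- 10% v 8%: 1.96 × √((0.0900 + 0.0736)/855) = 2.71 points. The interval is 2.0 ± 2.71, or -0.7 to 4.7, and includes zero.
- 5% v 3%: 1.96 × √((0.0475 + 0.0291)/855) = 1.86 points. The interval is 2.0 ± 1.86, or 0.1 to 3.9, and narrowly excludes zero. Because this is close, it was checked with whole counts (43/855 v 26/855): Newcombe gives 0.11 to 3.92 and the score interval 0.13 to 3.93. Both exclude zero.
- 10% v 5%: 1.96 × √((0.0900 + 0.0475)/855) = 2.49 points. The interval is 5.0 ± 2.49, or 2.5 to 7.5.

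The first two rows of a descriptive table would show the same 2-point gap, yet one gap is compatible with no difference and the other is not.

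**The case against.** Several counter-arguments have force.

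- **The information is not lost.** Counts and denominators by arm fully determine an unadjusted risk difference and its interval, and in a randomised trial that is a valid estimate. This stands. A reader might infer that the trial cannot say anything about which differences exceed chance, and that would be too strong. What is missing is a planned and reported estimate, adjusted as the other secondary outcomes are.
- **The text does not forbid an interval.** It says how the data will be presented. This also stands: the article plans only counts and percentages, which is weaker than permitting nothing else.
- **The two rules need not contradict each other.** A general rule followed at once by a paragraph on tolerability reads naturally as rule and exception, and estimates were promised only where presented. A reader might see an outright contradiction, but the wording does not support that. Even so, the exception leaves a comparative objective without a comparative estimate.
- **It is a detail for the full analysis plan.** That would hold if the article were silent. It states a method, so the choice is open to comment.
- **Descriptive reporting is defensible.** The reactions are expected, the safety profiles are described as well characterised, the reports are open-label self-report, and more intervals invite selective reading. These are sound reasons to avoid p values and to interpret with care. They do not count against a supportive risk difference with its interval, because the bare percentages carry the same reporting bias and also hide the sampling error.

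**Conclusion.** The point holds as a minor one. Tolerability is set up as a between-arm comparison, and the article's stated method for it yields no between-arm estimate or interval in the trial's own report. The practical consequence is limited: equal-looking gaps would go unlabelled as to whether they fit chance, as the 10% v 8% and 5% v 3% examples show. Those examples rest on assumed rates and on 855 participants per arm supplying side-effect data; fewer responders would widen the intervals.

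The primary analysis, sample size, conduct and data collection are unaffected, and no planned result would be wrong. The intervals address chance only. They do not remove any bias from unblinded self-report.

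**What to change.** In Analysis of outcome measures, keep the counts and percentages and add, for each of the six side effects and for any of the six, a between-arm risk difference with 95% CI. Adjust it as for the primary outcome, or use a score or exact interval where counts are small. Give no p values, label the results supportive, and note beside the table that the data are open-label self-report.

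The cost is a few lines of code and extra table columns, with no new data and no change to conduct. The downside is seven further intervals (six side effects plus the composite) without multiplicity control. The existing statement that secondary analyses are supportive already sets how they should be read.

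If the trial team prefers to stay descriptive, the alternative is to say explicitly that tolerability is an exception to the regression rule and to reword the objective, the outcome and the adverse-event text accordingly.
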